# INTRODUCTION

Despite significant improvement in the nutrition scenario over the past decades, the prevalence of child undernutrition in Bangladesh remains alarmingly high and infant and young child feeding practices, especially complementary feeding, are poor [[1](#_ENREF_1)]. The evidence available at the beginning of the A&T initiative in 2009 indicated that inadequate IYCF practices were the most important proximal determinants that contribute to the high burden of child undernutrition in Bangladesh and that nutrition education and behavior change communication were associated with improved IYCF practices*.* A recent study in Bangladesh had suggested that appropriate IYCF practices recommended by the WHO and UNICEF resulted in better growth of rural Bangladeshi infants and young children of 0-24 months of age [[2](#_ENREF_2)]. In Bangladesh, intensive nutrition education significantly improved the status of moderately undernourished children with or without supplementary feeding [[3](#_ENREF_3)]. An earlier study in Bangladesh also suggested that behavior change communication through trained counselors to promote and support breastfeeding was very successful – 70 percent of the mothers in the program areas breastfed their infants exclusively for 5 months of age compared to only 6 percent in the comparison areas [[4](#_ENREF_4)]. Although these were well-designed studies, these were efficacy studies. Evidence on the impact of large-scale programs to improve IYCF and nutrition in Bangladesh is less promising [[5](#_ENREF_5),[6](#_ENREF_6)].

Scaling up interventions to improve key direct determinants of undernutrition in Bangladesh, such as IYCF practices, are essential to accelerate progress toward reduction in undernutrition. Alive & Thrive’s portfolio of activities in this context has significant potential for impact. Rigorous impact evaluations are also essential to make contributions to the policy dialogue in Bangladesh and A&T’s impact evaluation fills a significant knowledge gap by examining impact at scale, using a rigorous evaluation design.

Alive & Thrive (A&T) is an initiative funded by the Bill & Melinda Gates Foundation to reduce undernutrition and death caused by suboptimal IYCF practices in three countries (Viet Nam, Bangladesh, and Ethiopia) over a period of six years (2009-2014). Alive & Thrive is led by FHI360 and is implemented through a partnership with Save the Children, GMMB, the International Food Policy Research Institute (IFPRI), and the University of California, Davis. In Bangladesh, this initiative is implemented in close partnership with BRAC and several other partners. A&T’s Bangladesh strategy is designed to support improvements in Infant and Young Child Feeding (IYCF) in three key ways: 1) improving policy and regulatory environments; 2) shaping IYCF demand and practice; and 3) increasing supply, demand, and use of high quality complementary foods. In order to achieve this, the A&T Bangladesh program has been divided into three main focus areas namely advocacy, community, and the private sector. In addition, a communications component is integrated into each of these focus areas to support their activities. The community-based model implemented by BRAC is a core initiative of the community model to provide quality nutrition counseling to women and families through home visits, to mobilize diverse members of the community and to bring media spots to media-dark areas.

# OBJECTIVES

The objectives of this impact evaluation are primarily to assess the impact of the package of A&T interventions delivered through the BRAC community-based platform that combines frontline health worker interventions and social mobilization. Using a pre-post cluster-randomized design with a comparison group (see below), our objectives are

1. To assess the impact of the BRAC-platform delivered interventions on IYCF practices among children 0-23.9 months of age;
2. To assess the impact of the BRAC-platform delivered interventions on stunting among children 24-47.9 months.

Having comparison areas that also receive other A&T interventions, such as the media campaigns, also allows us to capture shifts in IYCF practices, knowledge, norms, and perceptions over time that is due to those components alone. We will therefore also explore the use of data from the comparison areas, to generate evidence on the role of the media activities to shape demand and practice.

The impact evaluation is set up to address the following specific hypotheses:

1. Age-appropriate IYCF practices (EBF for 0-5.9 months or breastfeeding + age-appropriate complementary feeding for 6-23.9 months) will be better among children living in areas covered by the A&T intensive interventions (counseling, social mobilization and mass media) than those living in areas without the intensive interventions (only mass media).
2. Children 24-47.9 months of age in areas covered by the A&T intensive interventions will have lower levels of stunting than children 24-47.9 months of in areas with just the mass media intervention.

In addition to these objectives related to the community-based interventions, our design also allows us to assess the effects of the mass media campaign through the use of pre- and post-data collection at baseline and endline and the use of data on exposure to the mass media campaigns. We will use the extensive survey data to control for potential confounding in such analyses.

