# EVALUATION DESIGN

The impact evaluation of community component A&T interventions delivered through the EHC program uses a cluster-randomized design with repeated cross-sectional surveys at the baseline and endline (Figure 3). For the impact evaluation of A&T’s community-based rural platform, 20 rural subdistricts (*upazilas*) that were part of BRAC’s Essential Health Care (EHC) program platform for A&T were purposively chosen. The objective of this impact evaluation model is to capture the synergistic impact of A&T’s community component along with media communications and private-sector activities, such as the promotion and integration of micronutrient powders.

The impact evaluation is designed to capture impact on all key A&T indicators (stunting, infant and young child feeding (IYCF), and anemia). Using a repeated cross-sectional survey design, impact on stunting will be assessed in children 24-48 months old. The impact on other IYCF practices and anemia will be assessed in children 6-23.9 months old; and the impact on exclusive breastfeeding (EBF) will be assessed in children 0-5.9 months old. A double difference impact analysis as well as analysis by exposure level to interventions will be employed to determine the impact of A&T interventions.

The baseline survey was in April to July 2010, and an endline survey is planned for April to July 2014.

The main outcomes being examined are changes in mean height-for-age Z-score (HAZ) and changes in the prevalence of childhood stunting between baseline and the post-intervention survey. Other core impact indicators for A&T in Bangladesh include changes in age-appropriate WHO-recommended IYCF practices among children under 2 years of age (EBF for children 0-5.9 months old and breastfeeding + age-appropriate complementary feeding for children 6-23.9 months old) and anemia among children 6-23.9 months of age.

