**Table 4. Impact, process, and underlying factors captured by the baseline and endline household questionnaire**

| **Type of data** | **Questionnaire modules/questions** | **How used** |
| --- | --- | --- |
| Impact indicators | Child anthropometry  WHO-recommended IYCF indicators | Change between baseline and endline used to assess trends in impact indicators |
| Process data – client outcomes | Maternal IYCF knowledge  Awareness, trial, and adoption of key recommended practices  Behavioral determinants | Helps assess if IYCF knowledge shifted over project period, whether awareness of key recommended behaviors improved |
| Process data – client access, exposure, and utilization of services | Exposure to FLW counseling services and mass media  Utilization and coverage  Prenatal and postnatal care | Helps assess if exposure to intended program channels is as expected. Will also allow assessment of impact trends by levels of exposure to interventions |
| Influencing/underlying factors – child level | Child illness and health  Child development/milestones  Hygiene and hand washing | Helps assess if child-level factors modify influence of exposure to interventions. Child development milestones also function as an outcome/impact indicator in relation to IYCF practices and micronutrient powders. |
| Influencing/underlying factors –maternal level | Education, working condition, time constrains and child care arrangement.  Physical and mental well-being  Women’s status and maternal decision making power at the household | Maternal well-being is a prerequisite for intervention success. We would use these data to control for underlying mother factors and analyze the influence of mother constraints on ability to benefit from the A&T interventions. |
| Influencing/underlying factors – household level | Household SES (construction of SES scale from assets)  Household economic shocks  Household food security | Economic shocks could seriously undermine project impact. Additionally, improvements in SES over time could attribute greater impact to the project than is true. Therefore, data on SES, shocks, and food security are important both to control for these influences in analyses of change over time, as well as to examine the influence of household-level constraints on the ability to benefit from A&T interventions . |

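### The before-after change in the comparison areas cannot be attributed to media and other A&T components alone, because both arms receive mass media and no media-free arm exists

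*Combined protocol and SAP*

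**What the plan says.** The Objectives section describes the comparison group in these terms: "Having comparison areas that also receive other A&T interventions, such as the media campaigns". It says this arrangement "also allows us to capture shifts in IYCF practices, knowledge, norms, and perceptions over time that is due to those components alone", and announces exploratory use of comparison-area data to learn about the role of media. Later in the same section it adds that "our design also allows us to assess the effects of the mass media campaign through the use of pre- and post-data collection"; that sentence goes on to include individual media-exposure data, and the next promises control for confounding from the survey data.

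Hypothesis 1 sets out what each arm receives. The intensive areas have "A&T intensive interventions (counseling, social mobilization and mass media"), and they are compared with "those living in areas without the intensive interventions (only mass media").

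Evaluation Design allocates 20 sub-districts, 10 to each of two arms, and gives the aim of the evaluation model as to "capture the synergistic impact of A&T’s community component along with media communications and private-sector activities". Under Detailed statistical analysis approach, impact estimates are double differences between the arms. Table 4 warns that "improvements in SES over time could attribute greater impact to the project than is true" and gives this as a reason to collect and adjust for socioeconomic data.

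**The concern.** A before-after change in one group carries everything that altered over the four years between the 2010 and 2014 surveys. The section The Intervention describes national advocacy and national scale-up of feeding work alongside the media strategy, and all 20 sub-districts belong to the BRAC essential health care platform. None of this is separated from media by the allocation. The plan's statement that the shift is due to the A&T components therefore claims a property that the design lacks.

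What is at stake is the conclusion about media. The initiative's stated mandate includes passing on lessons so that others can replicate its cost-effective components, so a reader may use any component-level attribution directly.

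**Working it through.** The plan gives no figure to reproduce here. The question is which effects the arm-by-period data can identify.

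**Inputs.** Two arms of 10 sub-districts and two survey rounds (Evaluation Design); media in both arms (Hypothesis 1); double-difference estimator (Detailed statistical analysis approach). Assumption: media is absent at baseline and present in both arms at endline.

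**Cell means.** Let a be the comparison baseline level and d the baseline difference between arms. Let S be the change over time from every cause other than media and the community package (secular trend, advocacy, other services). Let M be the media effect, C the community-package effect without media, and I the media-by-community interaction.

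| | Baseline | Endline |
|---|---|---|
| Comparison | a | a + S + M |
| Intensive | a + d | a + d + S + M + C + I |

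There are four means and six parameters. The design matrix has rank 4, with these consequences:

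- Comparison-area change = S + M. Only the sum is estimable.
- Double difference = (S + M + C + I) − (S + M) = C + I. This is estimable and is the package effect given media.
- S, M, C and I separately, and M + C + I (everything against nothing), are not estimable.

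If the comparison-area change is X, then M = X − S. With X = 10 points and assumed S of 0, 10 or 15, M is 10, 0 or −5.

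**Illustration of size.** Suppose M = 0 and the whole change is secular. Inputs: exclusive breastfeeding 49.9% at baseline and intra-class correlation 0.12 (Table 3); 500 infants per arm per survey and a significance level of 0.05 (Sample size and power calculations; two-sided assumed). With 500/10 = 50 infants per cluster, the design effect is 1 + (50 − 1) × 0.12 = 6.88, and the effective n is 500/6.88 = 72.7. The same clusters are surveyed twice and the between-survey correlation is not given, so design effects of 1 and 6.88 are used as an assumed range.

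Probability of significance = Φ{[(p2 − p1) − 1.96√(2p̄(1 − p̄)/n)] / √([p1(1 − p1) + p2(1 − p2)]/n)}.

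For a 10-point rise, p1 = 0.499, p2 = 0.599 and p̄ = 0.549:

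- n = 500: (0.100 − 0.0617)/0.0313 = 1.22, giving 0.889.
- n = 72.7: (0.100 − 0.1618)/0.0821 = −0.75, giving 0.226.

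| Assumed secular rise | Design effect 6.88 | Design effect 1 |
|---|---|---|
| 5 points | 0.087 | 0.353 |
| 10 points | 0.226 | 0.889 |
| 15 points | 0.447 | 0.998 |
| 20 points | 0.695 | 1.000 |

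The sizes of rise are assumptions, because the documents state no secular trend.

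**Exposure-level analysis.** Within the endline round, exposed mothers have mean b1 + S + M and unexposed mothers b0 + S. The difference is M + (b1 − b0). A common S cancels, but the selection term b1 − b0 remains. Exposure is self-reported recall, and the recall threshold is left as an unspecified number of messages in the second plausibility analysis.

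**The case against.** The strongest reply is that the plan is more careful than one phrase suggests. The text refers to other A&T components with media as an example, and it calls the comparison-area work exploratory. It commits to individual exposure data and confounder control in the same section. Table 4, the Overall approach and the plausibility analyses plan to examine and adjust for changes in underlying determinants. Comparing exposed with less exposed mothers in the same round cancels a common trend, and having no unexposed clusters does not mean having no unexposed respondents. All of this stands. It reduces the problem, but adjustment reaches only measured factors, and the exposure comparison replaces the trend with self-selection. Neither supports attributing the shift to the components alone.

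A reader might infer that the plan will publish the whole comparison-area trend as a media effect. The documents do not support that: the statistical analysis plan never names the comparison-area change as a media estimator, and none of the three manuscripts in Publication Plans is devoted to media. Nor does the plan literally attribute the change to mass media alone.

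On synergy, the reply is that it is one descriptive sentence, with no hypothesis, indicator or interaction model behind it, and that Hypotheses 1 and 2 already state the right contrast. That also stands, so changing it is only a consistency edit.

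**Conclusion.** The attribution in Objectives is wrong as written and should be corrected. From arm and period alone, the comparison-area change equals media plus everything else that changed, and no split between them can be recovered. The documents supply no trend, so the bias in a before-after reading cannot be bounded. The 23% to 89% figure for a 10-point secular rise is conditional on that assumed rise and on the design-effect range.

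The limit applies to what may be concluded about media. It would be a mistake to read it as undermining the main result: both numbered objectives and both hypotheses concern the BRAC-delivered package on top of media, and the randomised double difference identifies that effect.

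**What to change.** 1. In Objectives, replace the clause that attributes the shifts to the components alone. State that change in the comparison areas combines media, national advocacy, other services and secular trend, and will be described, not attributed.
2. In the same section and in the exposure analyses, base any media inference on exposure-outcome associations within survey round, adjusted for village, socioeconomic status and access to media. Label these observational and exploratory.
3. For consistency, in Evaluation Design replace the reference to synergistic impact with the added impact of the community package given mass media. Package is the apt word because the Introduction says the BRAC community model also brings media spots to media-dark areas, so media dose may differ between arms.

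The cost is a causal claim about media that the design cannot support. Data collection, sample size and the primary analysis stay as they are.

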# THE INTERVENTION

## Description of the Alive & Thrive Program in Bangladesh

A&T’s mandate is to facilitate change for improved IYCF practices at scale; to document how interventions are delivered, how much impact can be achieved and at what cost, and to disseminate the evidence and lessons learned so that others can adapt and replicate the cost-effective components.

The goal of the A&T initiative is to reduce avoidable death and disability due to suboptimal IYCF. The specific objectives include an increase in exclusive breastfeeding (EBF) until 6 months of age and reduce stunting by delivering IYCF interventions to caregivers and families of children 0-24 months of age. A&T’s overarching model is based on the assumptions that sustainable improvements in breastfeeding and complementary feeding is achievable through strategies that improve the policy and regulatory environment to support IYCF interventions and practices.

The major goals of the A&T initiative in Bangladesh were to achieve the following in project areas:

1. Increase exclusive breastfeeding (EBF) by 49 percent (from 43 percent to 65 percent) among infants 0-5.9 months of age.
2. Reduce stunting by 10 percent (from 43 percent to 39 percent) among children of age 24-47.9 months.
3. Reduce anemia by 10 percent (from 50 to 45 percent) among children 6-23.9 months of age.

In Bangladesh, A&T’s comprehensive delivery model in Bangladesh largely consisted of a community component implemented through BRAC’s Essential Health Program (EHC) supported by a national advocacy component and a mass media communication strategy [[7](#_ENREF_7)]. A&T also worked in partnership with other local and international NGOs to intensify and scale up activities on infant and young child feeding (IYCF) at the national level as well as to guide the Government of Bangladesh (GOB) in mainstreaming nutrition into the five-year health sector plan. The A&T model also included efforts to actively engage private sector entities to broaden sources of investment for IYCF-related services. Advocacy component of the A&T focused on journalists, the press/media, medical and education sector leaders, and donors funding the next health sector strategy.

BRAC’s EHC program operates in several rural sub-districts *(upazilas)* of Bangladesh. The management structure of the A&T interventions, as delivered through through EHC is illustrated in Figure 1**.** Through the EHC platform, BRAC provides affordable and accessible health services to the poor through frontline workers (FLW): *Shasthya Shebika* (SS, community health volunteers) and their supervisors, the *Shasthya Kormi* (SK, community health workers). In EHC sub-districts, several cadres of workers help shape IYCF demand and practice. The SS and the SK were the front line service providers for A&T in 50 sub-districts with EHC programs who delivered age-appropriate IYCF counseling and support services during home visits, antenatal and postnatal sessions, and health forums. IYCF Promoters (PK) recruited for A&T interventions supported the IYCF work of the SS and SK. All of these FLWs were women. Mobile phones and monthly meetings were used to network these teams of workers within sub-districts and unions. All SS, SK and PK were expected to perform specific tasks during the household visits (Table 1) and were expected to give key messages for infants and young children of different age groups (Table 2).

Typically, SS visit about 250-300 households a month that have children aged 0-23.9 months to provide advice and services, attend monthly refresher training for a day once every month, and sell medicines. Each SK supervises 10-15 SS, prepares monthly registers for the SS, conducts field visits 6 days a week, attends monthly one-day refresher training and does performance review along with the SS, and comes to office one day each month to complete monthly report. The SK is also expected to visit all the households in her catchment area every 6 months. SK in sub-districts involved with BRAC’s EHC program receive an additional monthly honorarium for spending two extra hours per day on IYCF-related activities.

The IYCF promoters (PK) were expected to prepare household lists including children 0-23.9 months of age and pregnant women. Each PK was expected to start working from the residence of SS according to daily work schedule. The catchment area for PK was defined such that: (i) there were not more than 350 children 0-23.9 months of age; (ii) there were not more than 2500 households; and (iii) she could visit children 0-23.9 months of age once in two months.

To build an enabling environment for improved IYCF practices at the community, A&T program organizers addressed community constraints through awareness-building activities such as meetings and forums with husbands, religious leaders, MNCH committee members, pharmacists and shopkeepers, doctors, local council chairmen and members. A&T recruited 25 IYCF monitors to follow the performance of the SS, SK, and IYCF promoters. The monitors conducted a check on sampled households each month; the results determine incentives for each SS. Monitors were also expected to identify areas requiring strengthening. One A&T program organizer for each sub-district was recruited to supervise and monitor all IYCF activities, including home visits and counseling and also generation of community support. The existing upazila, district and regional managers were responsible for coordination among different BRAC programs and for liaison with other NGOs, private providers, and local government bodies and health staff.

Figure 1. Operational structure for Alive & Thrive in the BRAC Essential Health Care platform

Table 1. Responsibilities of SS, SK and IYCF Promoters during household visits in Alive & Thrive Program areas^[[1]](#footnote-1)^

| SS | SK | IYCF Promoter (PK) |
| --- | --- | --- |
| - Enters in her Register all identified pregnant women and children 0-24 months of age in her catchment area. - Immediately informs IYCF Promoters about any new births. - Advices mothers and the families to put the baby to the mother’s breast in one hour of birth. - Confirms giving the baby colostrum. - Encourages mothers and the families exclusive breast feeding (EBF) to the babies 0-6 months of age. - Identifies mothers having problems with EBF and solves, if possible; immediately informs IYCF Promoters about this and follows up if necessary. - Refers mothers having problems with feeding her child to appropriate places if needed for the problems. - Encourages mothers and the families regarding feeding children 7-24 months of age the family foods in addition to breast milk. - Identifies mothers having problems with feeding children 7-24 months of age the family foods in addition to breast milk, solves if possible; immediately informs IYCF Promoters about this and follows up if necessary. | - Conducts health forum. - Provides healthcare during household visits and ensures the following activities: - Follows up SS. - Encourages family planning methods for eligible couples. - Observes DOTS of suspected TB patients. - Pregnancy identification. - Encourages and provides ANC and PNC services to the pregnant women. - Encourages vaccination to the target children and pregnant women. - Registers new births. - Encourages installation and proper use of sanitary latrines. - Ensures use of safe drinking water. - Gives messages regarding importance of hand washing with soap for children and all family members. - Responsibilities during household visits - Registers 0-24 month children identified by SS. - Advices mothers and the families to put the baby to the mother’s breast in one hour of birth. - Advices mothers and the families to feed colostrums to the newborns. - Encourages mothers and the families EBF to the babies 0-6 months of age. - Identifies mothers having problems with EBF and solves, if possible; immediately informs IYCF Promoters about this and follows up if necessary. - Refers mothers having problems with feeding her child to appropriate places if needed for the problems. - Encourages mothers and the families regarding feeding children 7-24 months of age the family foods in addition to breast milk. - Identifies mothers having problems with feeding children 7-24 months of age the family foods in addition to breast milk, solves if possible; immediately informs IYCF Promoters about this and follows up if necessary. | - The household visit schedule of the IYCF Promoter – - 1st visit: within 48 hours of birth. - 2nd visit: within 7-10 days after birth. - 3rd visit: 2 month 1 day – 2 months 29 days. - 4th visit: 5 months 1 day – 5 months 29 days. - 5th visit: 6 months 1 day – 6 months 15 days. - 6th visit: 8 months 16 days – 9 months 15 days. - 7th visit: 12 months 1 day – 16 months 29 days. - 8th visit: 18 months 1 day – 23 months 29 days. - Visits households according to the schedule and - - Enlists children 0-24 months of age. - Encourages mothers and the families exclusive breast feeding (EBF) to the babies 0-6 months of age. - Encourages mothers and the families regarding feeding children 7-24 months of age the family foods in addition to breast milk. - Demonstrate appropriate techniques of feeding breast milk and other family foods to the mothers. - Problem solving related to breast feeding, feeding other family foods and follow up – - Holds forums with mothers regarding health and nutrition education. - If needed, works out of working hours for emergency situation. - Attends training, refresher training and meetings as needed. - Completes daily report forms, prepares monthly report of her catchment area and submits monthly reports to POs. |

Table 2. Key tasks for different age groups given by SS, SK and IYCF Promoters (PK) at household visits in Alive & Thrive program areas

| **0-5.9 months of age (0-180 days)** | **6 – 23.9 months of age** |
| --- | --- |
| - Demonstrate correct position and attachment of breastfeeding. - Follows up, if necessary, whether the infants are exclusively breastfed up to 6 months of age. - At 5.5 months of age, discuss with mothers and the families the importance of feeding family foods in addition to breast milk. - Prepares mothers and the family mentally to introduce family foods in addition to breast milk when the infants complete 6 months of age. | ***When the babies complete 6 months of age:***   - Discuss with mothers and the families the importance, quantity and preparation of family foods in addition to breast milk according to the age of the children. - Encourage mothers and the families to feed their children animal source foods (fish/meat/egg), milk products, fried/oily foods, colored vegetables, fruits and adding oil in foods of children. - Discuss with mothers and the families the quantity and density of daily foods of children.   ***When the babies complete 9 months****:*   - Discuss with mothers and the families that they should encourage their babies to eat by themselves. - Discuss feeding a sick child (frequent feeding, feeding child the foods that she/he likes). - Discuss importance of continuing breastfeeding up to 24 months of age in addition to family foods. |

##

